### Sample size calculation

Anticipating that a Cohen’s *d* of 0.40 would be realistic to determine effect size differences on the primary outcome between groups, based on previous study experiences [23–26], a sample size of *n* = 100 in each study group would have 80% power on two-tailed *t*-test calculations performed using G*Power software (Faul, Kiel) and an alpha error of 5%. Given an average attrition rate of 50% in online studies involving cannabis misusers [26], our final adjusted sample size is *N* = 450.

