### Data analysis

All analyses will be performed on an intention-to-treat basis and verified by complete case analyses. Imputation procedures will be chosen based on missing data patterns (e.g. using the MICE multiple imputation function in the statistical software package R and between 20 and 40 imputed datasets, depending on the extent of missing data, in accordance with suggestions made by Graham [47]). Moreover, study dropout analysis will be performed comparing participants who completed the follow-up survey against those who did not. Cohen’s *d* will be determined, with the significance threshold for all analyses defined as alpha = .05. The primary outcome—number of days of cannabis use over the preceding 7 days, estimated using the Time-Line-Follow-Back method—will be analysed by means of linear regression models with baseline characteristics and group allocation as predictors. Secondary outcomes will be analysed accordingly.

Since this will be a low-risk intervention, there will be no independent data monitoring committee. Study data will be analysed by the lead and the principal investigator after completion of data acquisition. Planned analyses are described in this section. There will be no formal stopping rules since we do not anticipate problems detrimental to participants. Data collection will be stopped when at least one hundred and fifty participants will be included in each group. The lead investigator and the principal investigator will make the final decision to terminate the data collection.

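### At the plan's own 50% attrition, N = 450 leaves 75 analysable participants per arm and about 68% power, not 80%; keeping 100 per arm would take 600

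*Protocol article*

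**What the plan says.** The protocol article, section Sample size calculation, takes a Cohen's d of 0.40 on the primary outcome between groups and a 5% alpha. It bases the size on "two-tailed *t*-test calculations performed using G*Power software" and concludes that "a sample size of *n* = 100 in each study group would have 80% power". With three arms that is 300 participants with outcome data. The next sentence makes the allowance for loss: "Given an average attrition rate of 50% in online studies involving cannabis misusers [26], our final adjusted sample size is *N* = 450".

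The resulting size is used again in the section Data analysis: "Data collection will be stopped when at least one hundred and fifty participants will be included in each group". Three groups of 150 make 450, so the two sections agree with each other. The section Recruitment of study participants gives a different required sample size, 300, which is the figure before any allowance for attrition. The section Randomization and trial flow fixes allocation at 1:1:1.

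**The concern.** An allowance for attrition should ensure that the number remaining after losses equals the number the power calculation needs. At 50% attrition the randomised number must therefore be twice the analysable number. Here it is only one and a half times as large. The multiplication is not written out, but 300 × 1.5 is exactly 450, which is what results when the loss is added as a percentage of the required number instead of being taken off the randomised number.

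The 80% is offered as the power for differences between groups on the primary outcome, and the Background states three pairwise effectiveness hypotheses: arm 1 against arm 2, and each of them against usual treatment. If the number analysed is smaller than the calculation assumes, the stated power is unsupported for all three. A null result, particularly for the effect of adding psychological support, would then be read as coming from a trial with 80% power when its own assumptions imply less. Because data collection ends by reference to 150 per group, the figure also determines how large the trial becomes.

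**Working it through.** **Inputs, all from the protocol article.** d = 0.40, two-tailed two-sample t-test, alpha 0.05, 100 per group for 80% power, attrition 50%, N = 450 (Sample size calculation); 1:1:1 allocation (Randomization and trial flow); at least 150 per group (Data analysis).

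**Step 1: reproduce the base figure.** With n per arm, the test statistic follows a noncentral t distribution with 2n − 2 degrees of freedom and noncentrality d√(n/2).

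- n = 99: power 79.97%.
- n = 100: noncentrality 0.40 × √50 = 2.83, power 80.4%.

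So 100 per arm is the smallest size that reaches 80%. The plan's base figure is correct and its inputs have been read as intended.

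**Step 2: apply the attrition.**

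- Expected to remain from 450: 450 × (1 − 0.5) = 225, or 225/3 = 75 per arm.
- Needed to retain 100 per arm: 100/(1 − 0.5) = 200 per arm, or 600 in total.
- Route that gives 450: 300 × (1 + 0.5) = 450.
- Attrition at which 150 per arm leaves 100: 1 − 100/150 = 33.3%.

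**Step 3: power at the number that remains.** For n = 75 the noncentrality is 0.40 × √37.5 = 2.45.

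| Randomised | Analysable per arm at 50% attrition | Power for d = 0.40 |
|---|---|---|
| 600 | 100 | 80.4% |
| 450 | 75 | 68.2% |
| 300 (figure under Recruitment) | 50 | 50.8% |

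A normal approximation at 75 per arm gives 68.8%, so the result does not depend on the method. Type II error rises from about 20% to about 32%. The smallest effect detectable with 80% power at 75 per arm is d = 0.46.

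**Step 4: what covariate adjustment could recover.** The planned primary analysis is a linear regression with baseline characteristics. If baseline 7-day use correlates r with follow-up use, and d = 0.40 is expressed on the unadjusted SD, the effective standardised difference is 0.40/√(1 − r²). The documents give no r, so the values below are assumptions. All are for 75 per arm.

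| Assumed r | 0.40/√(1 − r²) | Power |
|---|---|---|
| 0.3 | 0.42 | 72% |
| 0.4 | 0.44 | 76% |
| 0.5 | 0.46 | 80% |
| 0.6 | 0.50 | 86% |

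**The case against.** The case on the other side has five parts.

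1. **The ×1.5 step is inferred.** This is true; the article does not show it. The finding does not depend on it, because 450 fails to leave 100 per arm at 50% loss by whatever route it was reached. The article gives no other derivation and no lower attrition rate.

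2. **Attrition need not mean a missing primary outcome.** The article does not treat inactivity as dropout, sends repeated reminders followed by a phone call, asks those who withdraw about the primary outcomes, and pays vouchers for completed follow-up. Outcome data might therefore be obtained from more than half. This makes the 75 per arm conditional on the plan's own rate. It does not rescue the calculation, which uses 50% as the loss to be offset; the Limitations section also still expects relatively high dropout.

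3. **The primary analysis is not a t-test on completers.** It is an intention-to-treat regression with imputation where needed. Imputation alone does not restore the information in outcomes that were never observed. Adjustment for baseline use can gain precision, as shown above, so actual power may exceed 68%. How far depends on an unstated correlation and on whether d = 0.40 refers to the unadjusted SD. The Abstract describes the outcome as a change; if d already reflects that reduction in variance, the gain is smaller or nil. The 80% in the article comes from an unadjusted t-test and claims none of this.

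4. **150 per group is a minimum.** It is, but nowhere does the article plan for 200.

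5. **An article condenses the full protocol.** That would explain an omission. Here the inputs and the result are all stated, and they disagree.

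What stands is a limit on the wording: 68% is the power of the plan's own calculation at its own attrition rate, not a forecast for the adjusted analysis.

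**Conclusion.** The concern holds. Under the stated assumptions (d = 0.40, two-tailed t-test, alpha 5%, 50% of outcomes lost, equal arms), N = 450 gives 75 analysable participants per arm and 68.2% power, about 12 percentage points below the stated 80%. The shortfall against the intended size is 150 participants (600 − 450). The 80% would be right at 450 only with attrition of one third or less, which the article does not assume, or with a gain from baseline adjustment equivalent to a correlation of about 0.5, which it does not claim. The same shortfall applies to each of the three pairwise effectiveness comparisons. The figure of 300 under Recruitment of study participants is a separate inconsistency in the same chain; if it were the enrolment target, power at 50% attrition would be about 51%.

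**What to change.** Replace the attrition sentence in Sample size calculation with wording such as:

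> With 450 randomised (150 per arm) and 50% attrition, 75 participants per arm are expected to be analysable. This gives 68% power for d = 0.40, or 80% power for d = 0.46, in an unadjusted two-sided t-test at 5%. Retaining 100 per arm would require 600 randomised.

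In the same edit:

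- In Data analysis, state that baseline 7-day use days, already collected at t0, is always among the baseline characteristics in the primary regression. If a power gain from this is quoted, give it as a range over assumed correlations (72%, 76%, 80% and 86% for 0.3, 0.4, 0.5 and 0.6) and say that d refers to the unadjusted SD.
- Reconcile the 300 in Recruitment of study participants with the 450 and the 150 per group.
- If a loss of outcome data of one third or less was intended, say so and give the basis. The 450 would then be correct.

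The cost is a change of wording, a less favourable power figure and one covariate already in the data. No extra participants are needed if the lower power is accepted. Restoring 80% by numbers alone, at 50% attrition and without relying on adjustment, would mean randomising 150 more.

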### Data analysis

All analyses will be performed on an intention-to-treat basis and verified by complete case analyses. Imputation procedures will be chosen based on missing data patterns (e.g. using the MICE multiple imputation function in the statistical software package R and between 20 and 40 imputed datasets, depending on the extent of missing data, in accordance with suggestions made by Graham [47]). Moreover, study dropout analysis will be performed comparing participants who completed the follow-up survey against those who did not. Cohen’s *d* will be determined, with the significance threshold for all analyses defined as alpha = .05. The primary outcome—number of days of cannabis use over the preceding 7 days, estimated using the Time-Line-Follow-Back method—will be analysed by means of linear regression models with baseline characteristics and group allocation as predictors. Secondary outcomes will be analysed accordingly.

Since this will be a low-risk intervention, there will be no independent data monitoring committee. Study data will be analysed by the lead and the principal investigator after completion of data acquisition. Planned analyses are described in this section. There will be no formal stopping rules since we do not anticipate problems detrimental to participants. Data collection will be stopped when at least one hundred and fifty participants will be included in each group. The lead investigator and the principal investigator will make the final decision to terminate the data collection.

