**Methods:**

This study protocol describes a three-arm randomized controlled trial (RCT) comparing the effectiveness of three approaches, in terms of reducing cannabis use among problematic cannabis users, the first two treatment arms including the Spanish version of CANreduce 2.0 (an adherence-focused, guidance-enhanced, web-based self-help tool) (1) with and (2) without psychological support; and the third group (3) treatment as usual (TAU). Study hypotheses will be tested concerning the primary outcome: change in the number of days of cannabis use over the previous week, comparing assessments at 6 weeks and 3 and 6 months follow-up between groups and against baseline. Secondary outcomes related to cannabis use will be tested similarly. Mental disorders will be explored as predictors of adherence and outcomes. Analyses will be performed on an intention-to-treat basis, then verified by complete case analyses.

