### Randomization and trial flow

Once participants have completed their baseline assessment (*t*_0_), they will be randomized by a computer algorithm in a 1:1:1 ratio into one of three parallel groups and will be registered automatically in the background database. Participants’ internet protocol (IP) address will be monitored to prevent multiple registrations from one user attempting to have more than a single account or be allocated to a different group than originally assigned. Participants assigned to the control condition (TAU/study arm 3) will be remitted to a list with the treatment centres nearest their postal code. After 3 months in TAU, participants will gain access to CANreduce-SP without psychological support. The four assessment points of the study are depicted in Fig. 1. All subjects will be asked about their potential for using some different treatment during their participation in the study. A reminder e-mail will be sent before each assessment. It will contain information about the value of their answers, the estimated length of the questionnaire (in time to complete), and compensation for each evaluation to enhance the response rate. The same e-mail will be sent if there is no answer within 2 days and again after 4 days. One week after the last e-mail, participants will be contacted by phone and will be offered the option of completing the follow-up questionnaire verbally with an interviewer. Participants who drop out will be asked to answer a few questions pertaining to the two the primary outcomes and why they have decided not to continue in the study. Inactivity will not be considered a dropout criterion, due to the breaks that participants of web-based interventions commonly take. It is expected that some of these users will re-join the program later. A participant’s active withdrawal from the study will be the only dropout criteria. If possible, all data already gathered from these participants will be analysed. Figure 1 depicts the flow of subjects through the study.

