### Limitations

The first study limitation is related to inclusion criteria, in that cannabis users currently receiving other treatments to reduce cannabis consumption will be excluded. Second, all measurements will be self-reported and have not been validated in an online context, though they have largely been validated in other research and clinical settings. Third, as discovered in previous studies [24, 26, 50], we expect relatively high dropout rates. Finally, web-based studies tend to have low adherence rates, because of the distant nature of such interventions.

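### Complete-case analysis is named as the check on the intention-to-treat result, but with 50% attrition expected it cannot reveal dropout that depends on the unseen outcome

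*Protocol article*

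**What the plan says.** The Data analysis section of the protocol article sets the analysis principle and its check in one sentence: "All analyses will be performed on an intention-to-treat basis and verified by complete case analyses". The abstract repeats it: "Analyses will be performed on an intention-to-treat basis, then verified by complete case analyses".

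On the imputation itself, the same section says "Imputation procedures will be chosen based on missing data patterns". It offers MICE in R as an example, with "between 20 and 40 imputed datasets, depending on the extent of missing data". The primary outcome, days of use in the past seven, goes into a linear regression on baseline characteristics and group. A comparison of follow-up completers with non-completers is also planned.

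The Sample size calculation section shows how much data may be missing: "Given an average attrition rate of 50% in online studies involving cannabis misusers [26], our final adjusted sample size is *N* = 450". The Limitations section adds "we expect relatively high dropout rates".

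The Randomization and trial flow section describes repeat e-mails and a phone call to non-responders. It also says "Participants who drop out will be asked to answer a few questions pertaining to the two the primary outcomes". In that section only active withdrawal counts as dropout; inactivity does not.

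**The concern.** A check is useful only if it can fail when the main analysis is wrong. The main threat to an imputed analysis with half the outcomes missing is that, given everything recorded, non-responders differ from responders in their current cannabis use. Multiple imputation in its standard form assumes they do not. Complete-case regression assumes the same, or something stronger. When the two use the same covariates and only the outcome is missing, they are close to the same estimator, so they will agree whether or not the shared assumption is true.

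At stake is the wording of the trial's conclusion. A between-arm difference arising partly from who answered could be reported as verified. The article expects enough missing data for a modest departure to matter.

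**Working it through.** **Inputs from the protocol article.** d = 0.40, two-sided alpha 5%, 80% power, 100 per group, 50% attrition, N = 450 (Sample size calculation); 1:1:1 allocation (Randomization and trial flow).

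**Assumptions, not in the article.** The SD of weekly use days is 1.5 to 2.5. The size of any departure from missing at random is also assumed.

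**Reproducing the plan's figure.** For d = 0.40 the normal approximation gives 99 per group, and the noncentral t gives 80.4% power at 100 per group. The stated 100 reproduces. N = 450 is 150 per arm, so 50% attrition leaves about 75 responders per arm. Whether 450 is the right inflation is a separate matter; the 75 is used here only as what the plan's own figures imply.

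**Step 1: do the two analyses diverge when dropout is informative?** The simulation used 150 per arm in two arms, 50% missing, true effect zero, baseline-outcome correlation 0.5, and regression adjusted for baseline. Imputation used the same covariates with 20 datasets, over 1,500 replicates. In the informative setting, only the active arm's dropout depended on the unseen outcome, with log-odds 1.5 per SD.

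| Dropout | Complete-case mean (SD units) | MI mean (SD units) | Mean absolute gap, MI vs complete case | False positives, complete case / MI |
|---|---|---|---|---|
| Completely at random | -0.003 | -0.002 | 0.018 | 5.3% / 5.1% |
| Depends on baseline | -0.006 | -0.007 | 0.020 | 4.5% / 4.5% |
| Depends on unseen outcome, active arm | -0.411 | -0.411 | 0.017 | 86% / 84% |

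The gap between the methods is the same size in all three rows, so agreement does not separate the harmless settings from the harmful one. The third row is a deliberately strong scenario, chosen to show the mechanism; it is not a forecast.

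**Step 2: how large is the bias?** Let pA and pC be the missing proportions in the two arms, and δA and δC the mean amounts by which non-responders exceed their imputed values. Then

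true difference = estimated difference + pA·δA − pC·δC.

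With pA = pC = 0.5 this is the estimate plus 0.5 × (δA − δC). Starting from −0.40 SD:

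| δA − δC (SD) | 0 | 0.2 | 0.4 | 0.6 | 0.8 |
|---|---|---|---|---|---|
| True difference (SD) | −0.40 | −0.30 | −0.20 | −0.10 | 0.00 |

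Full cancellation needs 0.40/0.5 = 0.8 SD, which is 1.2, 1.6 or 2.0 days per week at SDs of 1.5, 2.0 and 2.5.

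If departures and dropout rates are equal in both arms, the difference stays at −0.40. With a common departure of 0.4 SD but unequal dropout, it moves either way: 60% active against 40% control gives −0.40 + 0.4 × 0.2 = −0.32, and the reverse gives −0.48.

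**Step 3: when is significance lost?** The standard error with 75 per arm is √(2/75) = 0.163 SD. The smallest significant difference is 1.96 × 0.163 = 0.32 SD. The tipping departure is (0.40 − 0.32)/0.5 = 0.16 SD, and slightly less with the t quantile, so about 0.15 SD. In days: 0.15 × 1.5 = 0.2 and 0.15 × 2.5 = 0.4 per week. This holds the standard error fixed and ignores any precision gained from baseline adjustment.

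**The case against.** The strongest reply is that sensitivity analyses for data not missing at random are detail that a journal article leaves to the full protocol or SAP, neither of which is shown. That stands against any claim that the trial lacks such an analysis, and none is made here. The point concerns what the article does state: which analysis serves as the verification. A further analysis elsewhere would not make that statement right.

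A second reply is that the article never says complete-case analysis is meant to detect informative dropout. Comparing imputed with complete-case results is a common look at how far the answer depends on the imputation. That is fair, and it is a reason to keep the comparison as description. It does not support calling the result verified.

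A third reply is that MICE is only an example and the imputation model is not described. Earlier follow-ups or website-use data could enter as auxiliary variables, and the two estimates could then differ. This also stands. A reader might infer that the comparison is wholly uninformative; that goes too far. It can show dependence on recorded variables, as can the planned completer versus non-completer comparison. Neither can show dependence on outcomes nobody recorded.

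Fourth, the reminders, phone completion, vouchers and questions to withdrawers may reduce the problem. They may, but the 50% attrition figure is still the plan's own. The questions to dropouts go to active withdrawers, so silent non-responders are not covered by them.

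**Conclusion.** The point holds as a fault in a stated method and should be corrected. The named check rests on assumptions no weaker than those of the analysis it is meant to verify, so it cannot support that claim for dropout tied to the unseen outcome. On the plan's own 50% attrition, an observed d = 0.40 would lose significance at a between-arm difference in departure of about 0.15 SD and would vanish at 0.8 SD. The figures in SD units assume about 75 responders per arm and equal attrition; those in days also assume an SD of 1.5 to 2.5.

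A reader might go further and infer that the result will be biased, because failing users leave the active arms while TAU participants stay to obtain the programme. The article does not support that. It does not report dropout by arm or tie TAU access to answering questionnaires, and it separates inactivity in the programme from dropout. Nor would that mechanism apply to arm 1 versus arm 2, which are described neutrally to participants. Bias in a contrast requires departures or dropout rates that differ by arm. That is possible here, but it is an assumption.

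**What to change.** In the Data analysis section and the abstract, drop the statement that complete-case analyses verify the result, and present them as a descriptive comparison.

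Name as the sensitivity analysis of the primary outcome a delta-adjusted multiple imputation:

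- Vary delta separately by arm for each pairwise contrast, including arm 1 versus arm 2. A common delta in both active arms would largely cancel in that contrast, which is the first listed hypothesis.
- Use steps of about 0.25 day from 0 to 2 days, keeping values within 0 to 7. A first step of 0.5 day would pass over the tipping point found above.
- Add one scenario that sets missing values to the participant's own baseline days.
- Report the delta at which the conclusion changes.
- Interpret the TAU contrasts at 6 weeks and 3 months separately from 6 months, when TAU participants have had the programme.

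Withdrawers' brief answers can help to judge which deltas are plausible, but only in part, because silent non-responders are not counted as dropouts.

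The cost is a few lines added to the imputation code and no new data. The downside is that the reported result may look less robust.

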#### Psychological support

Several elements of human support increase adherence (e.g. accountability to a coach who is considered trustworthy) [32]. As explained by Mohr\s supportive accountability, human support may be provided by a wide range of trained individuals [33]. The feedback received does not directly influence the treatment’s effectiveness but is more a strategy to highlight human support during the process. The goal is to increase confidence in the trainer and a sense that the trainer is concerned with the participant’s interests [33, 34]. This strategy increases the perception of legitimacy that would encourage people to respond to adherence demands actively. We provide automated human support through e-mails, videos, and reminders to both active groups. Besides this, we offer psychological support (feedback on demand) via personal contact with the e-coach to ask questions or express concerns via the internal message system or e-mail to increase this human support effect and evaluate the level of demand for this service.

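### Three unranked pairwise hypotheses, three follow-up visits, no primary visit and alpha = .05 throughout leave the primary false-positive rate uncontrolled

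*Protocol article*

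**What the plan says.** The Background section of the protocol article sets out three a priori superiority hypotheses on cannabis use: arm 1 (program with psychological support) over arm 2 (program without it), arm 1 over TAU, and arm 2 over TAU. None is ranked above another. A fourth hypothesis concerns adherence and is not part of this point.

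The Methods paragraph of the abstract says the primary outcome will be tested by "comparing assessments at 6 weeks and 3 and 6 months follow-up between groups and against baseline". The Background names the same three follow-ups. No section says which visit is primary.

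The Data analysis section gives linear regression with baseline characteristics and group as predictors, "with the significance threshold for all analyses defined as alpha = .05". It says that the planned analyses are described there. It gives no overall test, test order or adjustment, and does not say how the three visits enter the model.

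The Sample size calculation section assumes a Cohen's d "of 0.40 would be realistic to determine effect size differences on the primary outcome between groups" and concludes that "a sample size of *n* = 100 in each study group would have 80% power" with a two-tailed t-test at 5%.

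**The concern.** Read together, the hypotheses, visits and threshold give up to nine between-group tests of the primary outcome (three pairs at three visits), each at 5%. Nothing in the text limits how many false rejections this family can produce, and nothing says which test answers the primary question.

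The second problem matters as much as the first. If the visits disagree, the plan has no fixed way to resolve it. The visits also do not measure the same contrast. TAU participants receive the arm 2 program before the 6-month assessment, so a 6-month comparison with TAU is no longer a comparison with untreated controls. The lead and principal investigators both analyse the data and write up the results, so the plan should settle in advance which visit and which contrasts count.

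**Working it through.** **Inputs from the protocol article**
- Three pairwise hypotheses (Background); three follow-ups (abstract, Background).
- 5% threshold for all analyses (Data analysis).
- Two-tailed t-test, d = 0.40, 80% power, 100 per group (Sample size calculation).
- Randomisation "in a 1:1:1 ratio into one of three parallel groups" (Randomization and trial flow). With equal arms, two contrasts that share an arm correlate at 0.5 in absolute value.

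**Assumption.** The correlation rho of the primary outcome between follow-up visits is not given. I use 0.3 to 0.8, the same for every pair of visits, and show 0 and 1 as bounds.

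**Step 1: the plan's own figure.** The normal approximation gives n = 2(1.96 + 0.84)² / 0.40² = 2 × 7.85 / 0.16 ≈ 98.1, so 99 per group. The exact t-test needs 99.1, rounded up to 100. Power at 100 per group is 80.4%. The stated 100 therefore reproduces for one contrast tested at 5%.

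**Step 2: error rate under the global null.** For arm i at visit k, let X(i,k) be standard normal, independent between arms, with correlation rho between visits. Each contrast is Z = (X(i,k) − X(j,k)) / √2, rejected if |Z| > 1.96. With 1,000,000 draws per value of rho:

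| rho | 9 tests, two-sided | 7 tests (no 6-month TAU contrasts) | 9 tests, hypothesised direction only | 1 contrast, 3 visits |
|---|---|---|---|---|
| 0 | 32.4% | 26.8% | 18.5% | 14.2% |
| 0.3 | 30.9% | 25.8% | 17.2% | 13.6% |
| 0.5 | 28.5% | 24.2% | 15.8% | 12.5% |
| 0.7 | 25.0% | 21.7% | 13.9% | 10.9% |
| 0.8 | 22.6% | 19.9% | 12.5% | 9.8% |
| 1 | 12.2% | 12.2% | 6.6% | 5.0% |

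Three pairs at a single visit give 12.2% whatever rho is. Nine fully independent tests would give 1 − 0.95⁹ = 37.0%; the shared arms and repeated measurements bring this down.

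**Step 3: cost of controlling it at one visit.** The procedure is the overall 2-df F test at 5%, then unadjusted pairs only if it is significant. With three groups this holds the familywise error at 5%. If all three means are equal, the overall test must first reject, which happens 5% of the time. If exactly two are equal, only one true null remains, tested at 5%. Simulation under the global null gave 4.9% to 5.0%.

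Power per TAU contrast if both active arms beat TAU by d = 0.40:

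| Per arm | Unadjusted | Overall test, then pairs | Bonferroni over 3 |
|---|---|---|---|
| 100 | 80% | 76% | 66% |
| 75 | 68% | 62% | 51% |

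The 75 is 150 recruited per group × (1 − 0.50), from the plan's own recruitment target and attrition rate.

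**The case against.** **Scope.** This is a condensed article, and multiplicity is commonly left to a full protocol or analysis plan. A threshold sentence does not say that tests are unadjusted. That would answer a complaint about silence. Here, however, the text sets 5% for all analyses, says the planned analyses are in that section, and names three visits for the primary outcome. What it does fix is incomplete in a way that matters.

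**Number of tests.** Nine is an inference, because the regression description does not say how time enters. The Methods/design section also presents the late TAU data as a cross-over comparison, so the 6-month TAU contrasts may not have been meant as tests of the hypotheses. This stands, and is why the seven-test figures are given.

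**Direction.** A reader might infer that 23% to 31% is the chance of a false claim of benefit. It is not. The hypotheses are directional and a rejection the wrong way supports none of them. The rate for claims in the hypothesised direction is about half that.

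**Separate hypotheses.** Whether distinct pre-stated hypotheses need joint control is debated, and the plan does not say that any one significant contrast makes the trial positive. This has force across arms. It does not cover one hypothesis tested at three visits, which alone carries 10% to 14%.

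**Two stronger readings are not supported.** One is that the sample size does not match the testing plan. It does match in alpha and type of comparison: one pairwise test at 5% has 80.4% power at 100 per group. The other is that the hypotheses should have been ranked because the Psychological support section says "The feedback received does not directly influence the treatment’s effectiveness". That sentence goes on to describe support as a way of emphasising human contact. The Background and Discussion expect arm 1 to do better, and none of this affects type I error.

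**Conclusion.** The point holds. The primary outcome has no primary time point, and three unranked contrasts over three visits are all set at 5%.

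The size depends on the reading and on an assumed between-visit correlation of 0.3 to 0.8. It is about 23% to 31% for nine two-sided tests, 20% to 26% for seven, and 12.5% to 17% for nine counted in the hypothesised direction only (nominal 2.5% per test). The nine-test two-sided bounds are 12% at correlation 1 and 32% at correlation 0. All figures assume that no arm differs at any visit.

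The conclusion does not rest on the correlation, because one visit alone gives 12.2% over the three pairs. It should be fixed before the data are analysed. It does not invalidate the design or the per-contrast sample size.

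**What to change.** In the Data analysis section:
1. Name 3 months (t2) as the primary time point. The article times TAU access differently in different places (18 weeks after baseline in Methods/design; after 3 months in Randomization and trial flow; following the t2 assessment in Control condition). Every version puts it after t2, so t2 is the last visit with all three arms as randomised.
2. At t2, run the 2-df overall test of group at 5%. Test the three pairs at 5% each only if it is significant.
3. Report 6 weeks, 6 months and all secondary outcomes as supportive, with confidence intervals.
4. Restate power for this procedure.

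Other choices would also control the error. The 6-week visit, at program end, is a possible primary visit, and Bonferroni over three pairs is valid but costs more power. What matters is that one rule is fixed in advance.

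The cost is wording plus some power: about 4 percentage points per TAU contrast at 100 per arm (80% to 76%) and about 6 at 75 per arm (68% to 62%), if both active arms beat TAU by d = 0.40. No new data are needed.
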